#### Secondary outcomes

The technical success rate of RIC (defined by the rate of scope passage at the dilation site just after completion of RIC)Improvement in subjective symptoms, which will be evaluated using the visual analog scale (VAS) or the Crohn’s disease activity index between before and after RICDuration of hospitalizationProcedure time of RIC which is from the start to the end (completion of dilation) of RIC

We have selected these secondary outcomes to evaluate the feasibility and efficacy of performing RIC in the small intestine in this trial.

### Data collection

All data will be entered electronically using a case report form which includes age, sex, an underlying disease which contributed the to the formation of stenosis, medication, past history, smoking history, examinations to evaluate eligibility (including laboratory data, radioscopy, endoscopy, computed tomography, magnetic resonance imaging, and abdominal ultrasound), pictures, and movies of RIC. That information is considered reliable and valid to evaluate the feasibility and safety of RIC for the small intestine.

### Data management and statistics

As with data collection, standard processes will be implemented to improve the accuracy of data entry and coding. A formal hypothesis testing is not appropriate because this is a pilot study to investigate the feasibility and safety of RIC for the small intestine with a small sample size. Descriptive statistics for primary and secondary outcomes described above will be conducted. We will evaluate the improvement of subjective symptoms between before and after RIC using Student’s *t* test and presenting 95% confidence intervals.

### The study procedure and schedules

The SPIRIT checklist was followed as a guide for reporting this study protocol. It is shown in Table 1. The populated SPIRIT checklist is also provided as an additional file (see Additional file 1). We will target and screen those patients who present with subjective symptoms such as abdominal bloating, vomiting, and ileus. Most of the screening examinations will be clinical. Abdominal ultrasound or magnetic resonance imaging will be employed to investigate the wall thickness at the stenotic site as much as possible. The investigators will explain the procedure of the trial to those patients who meet the criteria and will obtain written informed consent. Participants will be able to withdraw their consent to participate whenever they want. Patients’ registration will be performed using the eligibility confirmation sheet. This pilot study is a single-arm non-randomized trial; therefore, the enrollment will be accomplished after filling out the confirmation sheet.

The enrolled participants will undergo the RIC procedure and will stay admitted to the hospital for around 7 days after RIC. Follow-up will be conducted after 1 month. The occurrence of any adverse events (AEs) will be monitored during this time. Subjective symptoms including abdominal bloating, abdominal pain, and nausea will be evaluated using VAS.

### Randomization and blinding

Not applicable.

### Safety

As mentioned above, the safety of RIC is the primary outcome of this study. Bleeding and perforation after RIC are the probable major AEs. Our previous report and other studies showed that delayed bleeding and perforation were the major AEs. The participants could also develop pancreatitis after EBD via the transoral approach. These AE and other complications will be monitored until 1 month after RIC and recorded in a case report form.

Serious adverse events (SAEs) are defined as follows:All deaths and immediate life-threatening events, whether related or unrelated to the procedureProlongation of hospitalizationSubstantial disruption of normal life functions

All SAEs will be recorded as well and reported to the institutional review board and the Ministry of Health, Labor and Welfare as soon as possible.

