### Population

We will include 10 patients with small bowel stenosis. This is a pilot study to investigate the safety and feasibility of RIC for small bowel stenosis; thus, the number of patients should be as small as possible. However, a certain number of participants are necessary to evaluate the safety and feasibility. Therefore, we have set the number of patients that comprise the study population at 10.

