### Outcomes

#### Primary outcome

The primary outcome of this study is the safety of using RIC for benign stenosis in the small intestine, and the safety is evaluated by measuring the frequency of adverse events of special interest (AESI) during 1 month after RIC. AESI includes complications related to RIC, such as delayed bleeding and perforation, which require endoscopic hemostasis or surgery. Safety of RIC is selected as the primary outcome because this is a pilot study and there are no other studies reporting the safety of performing RIC in the small intestine using BAE.

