## Discussion

This paper describes the protocol for a pilot study that explores the safety and feasibility of RIC for small bowel stenosis. To the best of our knowledge, there are no reports in which RIC is performed for benign stenosis in the small intestine using BAE. Our previous study [14], the ongoing trial, and other studies target those lesions that are located in the colon and terminal ileum where a colonoscope can reach easily. The RIC technique, according to the previous studies [14, 16, 19, 20], could provide several benefits such as larger dilation and a shorter hospital stay when compared to EBD. However, we are unable to obtain the long-type electric knife, which has enough length so that RIC can be performed in the small intestine using BAE. If we are able to adapt this RIC technique for small intestinal stenosis for which BAE is required, surgery could be avoided in these patients. We have performed the RIC technique in over twenty patients, and it was successful in all the cases. Therefore, we may be able to perform this technique without encountering significant technical challenges.

On the contrary, RIC showed a relatively high frequency of delayed bleeding compared to EBD (8.8 vs. 0%) [19]. This important issue should be addressed in the future. Therefore, we selected the safety of RIC as a primary outcome in this pilot study. We can evaluate the safety by investigating AESI during the 1-month follow-up after RIC. We hope that this pilot study would be useful in establishing the safety of RIC for small bowel stenosis. If we are able to confirm that performing RIC in the small intestine is relatively safe, we will conduct a continuous study with a larger number of patients.

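### The SAE definition counts a prolonged hospital stay but not a new admission, so a readmission after discharge is not an SAE on that ground alone

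*Protocol article*

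**What the plan says.** The Safety section introduces the SAE criteria as a definition, with no wording that marks them as examples. The first item covers deaths and immediate threats to life. The rest of the list reads "whether related or unrelated to the procedureProlongation of hospitalizationSubstantial disruption of normal life functions" (the line breaks between items were lost when the text was extracted). The only item that mentions hospitalization is the one on prolongation.

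The same section states what follows from the label: "All SAEs will be recorded as well and reported to the institutional review board", and also to the Ministry, without delay.

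Three other places set the context:

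- **Hospital stay.** Under The study procedure and schedules, participants "will stay admitted to the hospital for around 7 days after RIC". Table 1 puts the Day 7 visit in hospital and the Day 28 visit out of hospital.
- **Safety window.** The Safety section says of bleeding, perforation and pancreatitis: "These AE and other complications will be monitored until 1 month after RIC and recorded in a case report form".
- **Primary outcome.** AESIs are counted over one month after radial incision and cutting (RIC). They are complications related to RIC, "such as delayed bleeding and perforation, which require endoscopic hemostasis or surgery".

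**The concern.** A hospitalization criterion limited to prolongation works only while the patient is an inpatient. Here the planned stay covers about the first week of a four-week safety window. In the remaining weeks a patient may have to come back into hospital for a complication of the procedure, and the return itself meets no listed criterion.

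The Safety section names delayed bleeding and perforation as the major adverse events to expect. The Background reports that delayed bleeding in the group's ongoing study was controlled endoscopically in every case without transfusion. A bleed of that kind could lead to readmission without being an immediate threat to life.

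At stake is whether such an event is classed as serious, and so whether it goes promptly to the review board and the Ministry while the trial is still enrolling. That matters more than usual here, because the knife is not approved in Japan and the trial's main question is safety.

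**Working it through.** The article gives no figure on this point to reproduce. The check is a comparison of the stated rules and one simple proportion.

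**1. One event, two dates.** Take a delayed bleed treated by endoscopic hemostasis, not immediately life-threatening.

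| | Before discharge (say Day 6), stay extended | After discharge (say Day 10), patient readmitted |
|---|---|---|
| Death or immediate threat to life | No | No |
| Prolonged hospitalization | Yes | No: no current stay to prolong |
| Disruption of normal life functions | A matter of judgment | A matter of judgment |
| SAE on hospitalization grounds | Yes | No |
| AESI in the primary outcome | Yes | Yes |
| Recorded in the case report form | Yes | Yes |

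The two events differ only in timing relative to discharge. The later one required a new admission, yet it is the one that the hospitalization item does not reach.

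**2. How much of follow-up is exposed.** Inputs are a planned discharge around Day 7 (The study procedure and schedules) and a last scheduled visit on Day 28 (Table 1).

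Share after discharge = (end of follow-up − discharge day) / end of follow-up

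- Day 7 and Day 28: (28 − 7)/28 = 21/28 = 75%.
- Day 7 and a 30-day month: (30 − 7)/30 = 23/30 = 77%.
- Assuming that discharge may fall on Days 5 to 9 and follow-up may end on Days 26 to 30: from (26 − 9)/26 = 17/26 = 65% to (30 − 5)/30 = 25/30 = 83%.

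On any of these readings, most of the window lies after discharge.

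**3. How likely the type of event is, for context.** The Discussion cites delayed bleeding of 8.8% with RIC in an earlier study. The Population section sets 10 patients. If that rate applied here and patients were independent, the chance of at least one delayed bleed would be 1 − (1 − 0.088)^10 = 1 − 0.912^10 = 0.602, or about 60%. The rate comes from elsewhere in the bowel, since the Discussion says that earlier studies treated the colon and terminal ileum. The article does not say what share of bleeds occurs after discharge or leads to readmission. The 60% is therefore not the chance of a misclassified event, which cannot be computed from the article.

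**The case against.** Four points can be made on the other side, and much of each stands.

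**The other two items still apply after discharge.** A reader might infer that a late readmission for bleeding or perforation can never be an SAE. The text does not support that. A perforation or a severe bleed may well be immediately life-threatening, and readmission for urgent hemostasis could be read as a major disruption of normal life. What remains is that classification then depends on an undefined judgment, whereas an extended first stay qualifies automatically.

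**The safety result does not lose these events.** A reader might infer that the primary outcome is undercounted. It is not. The AESI definition applies for the full month wherever the patient is, and surgery and endoscopic hemostasis are named in it. All complications in the month are also recorded. Nor is an SAE rate a primary or secondary outcome, so no stated endpoint is biased by the gap.

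**Oversight may not rest on SAEs alone.** A reader might infer that the review board and the Ministry receive nothing but SAEs. The article does not say so. It says that SAEs go to them promptly and is silent on other events. The Monitoring section also has a designated monitor follow adverse events without limiting this to serious ones. What stands is narrower: SAEs are the only category for which the article states prompt reporting.

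**The article is a condensed text.** The full protocol may hold a complete definition. But this is not a detail left out. The article states the definition and states it as complete. If the full protocol includes new hospitalization, the article misreports it and should be corrected.

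**Conclusion.** The point holds in a limited form. The stated SAE definition omits new hospitalization. After planned discharge, which leaves about 75% of follow-up days (65% to 83% under the varied dates), a readmission for delayed bleeding or perforation is not an SAE by virtue of the readmission. It becomes one only through the life-threatening or life-disruption item. The practical effect is that a readmission that is not life-threatening is not assured of SAE status, nor of the prompt report to the review board and the Ministry that goes with it.

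The conclusion rests on reading the list as closed, as it is written, and on discharge taking place at about Day 7. The 75% is a share of calendar days, not of risk. The documents give no timing for delayed bleeding, so the number of events affected is unknown. The AESI analysis stands as planned.

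**What to change.** Replace the hospitalization item in the Safety section with *new (unplanned) hospitalization or prolongation of existing hospitalization*. The item then covers the whole 28 days instead of about the first 7, and the same complication is treated alike before and after discharge.

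Two additions are optional: an item for events needing surgery or another intervention to prevent permanent harm, which would largely overlap with the AESI definition, and a sentence saying what counts as prolonging the planned stay.

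The cost is a one-line amendment and at most a few more expedited reports among 10 patients. Sample size, outcomes and analysis do not change. If the full protocol already has the wider definition, only the article needs correcting.

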### Monitoring

The principal investigator will designate a monitor to survey if the investigators obey the study protocol. The monitor will also survey the safety and adverse events of study participants.

## Discussion

This paper describes the protocol for a pilot study that explores the safety and feasibility of RIC for small bowel stenosis. To the best of our knowledge, there are no reports in which RIC is performed for benign stenosis in the small intestine using BAE. Our previous study [14], the ongoing trial, and other studies target those lesions that are located in the colon and terminal ileum where a colonoscope can reach easily. The RIC technique, according to the previous studies [14, 16, 19, 20], could provide several benefits such as larger dilation and a shorter hospital stay when compared to EBD. However, we are unable to obtain the long-type electric knife, which has enough length so that RIC can be performed in the small intestine using BAE. If we are able to adapt this RIC technique for small intestinal stenosis for which BAE is required, surgery could be avoided in these patients. We have performed the RIC technique in over twenty patients, and it was successful in all the cases. Therefore, we may be able to perform this technique without encountering significant technical challenges.

On the contrary, RIC showed a relatively high frequency of delayed bleeding compared to EBD (8.8 vs. 0%) [19]. This important issue should be addressed in the future. Therefore, we selected the safety of RIC as a primary outcome in this pilot study. We can evaluate the safety by investigating AESI during the 1-month follow-up after RIC. We hope that this pilot study would be useful in establishing the safety of RIC for small bowel stenosis. If we are able to confirm that performing RIC in the small intestine is relatively safe, we will conduct a continuous study with a larger number of patients.

### Limitation

The number of patients in this trial is small because this is a pilot study.

### Trial status

This trial study has been approved. We plan to start recruitment in January 2021 and end it in June 2024.

## Data Availability

Data available on request from the authors.

## Abbreviations

AE: Adverse events
AESI: Adverse events of special interest
BAE: Balloon-assisted endoscopy
EBD: Endoscopic balloon dilation
ESD: Endoscopic submucosal dissection
RIC: Radial incision and cutting
SAE: Serious adverse event
VAS: Visual analog scale
